### Intervention

The interpretation of respiratory function tests and biomarkers will be performed by the principal investigator pulmonologist at each centre or by trained designated collaborating pulmonologists by following these models:

High-risk inflammatory asthma is defined by FeNO ≥25 ppb or BEC ≥300 cells/µL in participants ≥12 years (≥20 ppb or ≥300 cells/µL in children aged 6 to <12 years)^15 50^ : one or more elevated biomarkers will be interpreted as a high risk of asthma exacerbation. If spirometry is non-diagnostic, BPT will be prioritised (<2–4 weeks).Low risk inflammatory asthma is defined by FeNO <25 ppb and BEC <300 cells/µL (<20 ppb or <300 cells/µL in children aged 6–<12 years)^15 50^: this will be interpreted as a low risk of asthma exacerbation. If spirometry is non-diagnostic, BPT will be scheduled according to the standard waiting list.

Results of biomarkers will be integrated on the medical report indicating the probability (high/low) of asthma exacerbation and suggested management with either ICS taken as-needed (T2-low) or regularly (T2-High) ICS if clinically appropriate, which will be forwarded to the referring physician.

The patient test pathway based on their respiratory test and the results of the inflammometry assessment is summarised in figure 2.

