### Statistical methods

Data will be independently analysed by a biostatistician from the CHUS using R software (V. 4.2.0 or later, R Foundation for Statistical Computing, Vienna, Austria) in collaboration with a health economist. Missing data will be documented, and multiple imputation by chained equations will be considered for data missing at random when <20% of data is missing. Statistical significance will be determined using a two-sided alpha level of 0.05. Adjustments for multiple comparisons with the Benjamini-Hochberg procedure will be applied where necessary, including for subgroup analyses on the primary outcome.^51^

All primary analyses will also be stratified by pre-specified subgroups: study site, age categories (6–<12 years, 12–<18 years, ≥18 years), biological sex, ethnicity, smoking status and other potential confounding variables related to inflammatory biomarker measurement. Additionally, we will perform sensitivity analyses excluding active smokers. Categorical variables will be presented as counts with corresponding percentages, while continuous variables will be reported as either means with standard deviations (for normally distributed data) or medians with interquartile ranges (for non-normally distributed data). For comparative analyses between groups, we will employ independent t-tests or Mann-Whitney U-tests for continuous variables based on distribution, and χ^2^ tests or Fisher’s exact tests for categorical variables, as appropriate based on expected cell frequencies.

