For the primary outcome of waiting time differences, the baseline diagnostic delay, prior to the project implementation, will be established based on the time elapsed between the initial request for an asthma diagnostic test made by primary care and the performance of that test. During the intervention, diagnostic delays will be monitored prospectively, both overall and stratified by inflammatory status. We will apply linear mixed-effects models with restricted maximum likelihood estimation. These models will incorporate (high-risk vs low-risk), study period at time of inclusion, and the number of awaiting tests as fixed effects. Random effects will account for within-centre clustering and repeated measurements. In addition, Kaplan-Meier survival curves will be constructed to visualise the probability of remaining undiagnosed over time for both high-risk and low-risk inflammatory phenotypes. These curves will allow for a graphical representation of differences in diagnostic efficiency between groups. Cox proportional hazards regression will be used to identify significant predictors of waiting time with HRs and 95% CIs reported.

Diagnostic performance in the secondary outcome will be evaluated through ROC analysis, calculating the area under the curve (AUC) with 95% CIs for each individual marker and for their combined use. Sensitivity, specificity, positive and negative predictive values and likelihood ratios will be calculated with their respective 95% CIs.

Health utility values will be derived from EQ-5D questionnaires^39 52 53^ completed at baseline and follow-up visits. Quality-adjusted life years will be calculated using the AUC method, connecting utility values across measurement time points. This approach integrates health-related quality of life over the 12-month follow-up period. To assess the financial implications of implementing FeNO testing within the provincial healthcare framework, we will develop a budget impact model for the MSSS. Environmental and satisfaction-related outcomes will be analysed using descriptive statistics. CO₂ emissions from inhalers dispensed to non-asthmatic individuals will be estimated based on Cascades Canada data,^27^ and patient satisfaction with inflammometry will be assessed using structured questionnaires.

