### Sample size

Approximately 3000 diagnostic tests for suspected asthma are currently pending across the three participating centres (CHUS, CHUSJ and MCH), including around 1500 paediatric tests. Propulsion Santé was funded for 12 months of full-time recruitment (convenience sampling). Based on this pre-existing waitlist and expected referral rates, the Propulsion Santé study aims to recruit 1500 participants aged 6 years and older in the three centres. This sample size will allow us to detect a minimal effect size of 0.07 (Cohen’s f), assuming a significant level of 5%, a power of 80% and a correlation of 0.5 among repeated measures. The calculation was performed using a power analysis for a repeated measures ANOVA with a between-subjects factor in G*Power v 3.1.9.4. Of course, this sample size exceeds our minimum requirement, providing greater assurance in detecting the expected effects, but will also provide a unique opportunity to evaluate diagnostic delays and outcomes in real-world conditions. In addition, the findings will contribute to an ongoing meta-analysis on the diagnostic performance of inflammatory biomarkers.^54^

For the DIVE and DIVE 2 translational substudies (designed prior to PROPULSION SANTÉ), a sample size of 123 participants was originally calculated to provide 90% power to assess the diagnostic performance of three ROC curves. The sample size assumes a 2:1 ratio of asthma-positive to asthma-negative participants, allowing the analysis of three ROC curves, each targeting area under the curve (AUC) values ≥ 0.7, which are significantly different from the null hypothesis (AUC = 0.5), using a two-sided alpha level < 0.016, adjusted for multiple comparisons across three biomarkers.

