### Discussion

This study addresses a critical gap in the literature by prospectively evaluating the implementation of inflammatory biomarkers in a real-world primary care referral pathway across both adult and paediatric populations. Beyond its scientific contribution, our protocol will optimise clinical resources by reducing the backlog of approximately 3000 respiratory function tests, currently awaiting completion across the three participating centres, through the engagement of study-dedicated respiratory therapists.

We anticipate that this study will demonstrate the utility of inflammatory biomarkers as effective triage and prioritise instruments for BPT. Given the high rate of false positives in respiratory testing as well as the substantial rate of clinical misclassification in Canada (between 33% and 45% in adults and children),^20 22^ our study will calculate optimal biomarker thresholds to achieve 90% specificity, positive predictive value (PPV) exceeding 80% and LR+ greater than 10—parameters essential for reliable diagnostic confirmation.^57^ In effect, this strategy sacrifices sensitivity in favour of specificity, leading to high PPV and LR+.

Existing literature supports the relevance of our approach. Li *et al* conducted a large retrospective cohort study involving 7463 adult patients with suspected asthma in secondary care. Among the 2349 patients with complete biomarker data, concurrent elevation of FeNO (> 40 ppb) and BEC (>0.3×10ˆ9 cells/L) was associated with a diagnostic specificity greater than 95%.^58^ Similarly, Nekoee *et al* demonstrated that combining biomarkers with spirometry improved diagnostic accuracy (AUC 0.82, 95% CI 0.78 to 0.86),^59^ reinforcing the relevance of inflammometry in routine assessment. Additionally, the predictive value of both BEC and FeNO has been demonstrated in adults,^812 15 16 19 60^,^70^ and to a lesser extent in the paediatric^50^ populations, with significant clinical implications for early intervention and treatment adjustment. Furthermore, these biomarkers are valuable tools for therapeutic decision-making, as elevated values are associated with a better response to anti-inflammatory therapies.^71^,^75^ As modifiable indicators, the inflammatory signals provided by BEC and FeNO highlight the importance of early measurement to better prioritise patients requiring timely inflammation control.^15 61 62 64^

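### The primary mixed model lists risk class and queue length as main effects only, although the scheduling rule makes the class difference grow with the queue, so one coefficient averages over a difference that the plan itself expects to change

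*Protocol article*

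**What the plan says.** The Statistical methods section of the protocol article fixes the form of the primary analysis: "We will apply linear mixed-effects models with restricted maximum likelihood estimation", and then "These models will incorporate (high-risk vs low-risk), study period at time of inclusion, and the number of awaiting tests as fixed effects". Random effects cover centre and repeated measurements. No interaction is listed, and the residual variance structure is not stated.

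The Intervention section sets the rule that produces the delays. After non-diagnostic spirometry, a high-risk patient is prioritised for BPT within roughly two to four weeks. For a low-risk patient, "BPT will be scheduled according to the standard waiting list".

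The Introduction reports about 3000 pending tests and waits of more than a year. The Discussion expects this to change: "our protocol will optimise clinical resources by reducing the backlog of approximately 3000 respiratory function tests".

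**The concern.** The queue acts on the two classes in different ways. Between spirometry and BPT, a low-risk patient's wait is the queue, whereas a high-risk patient bypasses it. On that leg the slope of delay on the number of awaiting tests is near zero in one class and steep in the other. A model with main effects only gives both classes the same queue slope and returns the same class difference at every queue length.

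This matters because queue length is a covariate that the plan expects to move during the study, and because the Conclusion presents the strategy as scalable. A centre considering adoption needs the gain at its own list length, and one average over this study's queue does not provide it.

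A secondary consequence concerns precision. The rule compresses BPT waits in the high-risk class and leaves them spread out in the low-risk class. If the model is fitted with a common residual variance, the interval for the class difference can be miscalibrated when the classes are unequal in size.

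**Working it through.** **The plan's own figure.** The only number attached to the primary comparison is in the Sample size section, for 1500 participants: "This sample size will allow us to detect a minimal effect size of 0.07". The measure is Cohen's f, and the stated inputs are two-sided alpha 5%, power 80% and a within-person correlation of 0.5. For a between-subjects factor in repeated-measures ANOVA, lambda = f² × N × m / (1 + (m − 1) × rho), with k − 1 and N − k degrees of freedom. The article does not give k (groups) or m (measurements). With N = 1500 the minimal f is 0.0724 (k = 2, m = 1), 0.0695 (k = 3, m = 2) or 0.0697 (k = 4, m = 3), all of which round to 0.07. With k = 2 and m = 2 to 4 it is 0.0627 to 0.0572, so 0.07 is then conservative. The figure concerns an average class difference and does not bear on queue dependence.

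**Inputs from the document.** High-risk BPT wait: about 3 weeks, the middle of the stated window. Share with non-diagnostic spirometry: up to 80%, and over 60% in children (Introduction). Queue: about 3000 tests in three centres, so about 1000 per centre if evenly split.

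**Assumptions.** A list of 1000 takes about 52 weeks, that is 19.2 tests per week. All patients start with spirometry. The queue falls during the year to 800 or to 300 per centre; the document gives no final value.

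**Class difference at queue length q.** High minus low = p × (3 − q / 19.2), where p is the non-diagnostic share. The wait before the first visit counts in both classes and cancels.

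| Waiting per centre | Low-risk BPT wait (weeks) | Difference, p = 0.8 | Difference, p = 0.6 |
|---|---|---|---|
| 1000 | 52.1 | −39.3 | −29.4 |
| 800 | 41.7 | −30.9 | −23.2 |
| 650 | 33.9 | −24.7 | −18.5 |
| 300 | 15.6 | −10.1 | −7.6 |

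**What the additive model returns.** In simulations with 1500 patients in three centres, and with class unrelated to queue, the additive coefficient was −24.7 weeks for a fall from 1000 to 300 (p = 0.8), against an average true difference of −24.6. For a fall from 1000 to 800 it was about −35.0 against −35.0. It recovers the difference near the mean queue and says nothing about either end. If the high-risk share drifts by 30 percentage points over the year, the coefficient can miss the average by up to about 1.5 weeks.

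**Precision under a common residual variance.** Let s be the standard deviation of the wait before the first visit, L the mean low-risk BPT wait and h the high-risk share. Assume p = 0.8 and a standard deviation of 8 weeks for the low-risk BPT wait.

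- High-risk variance: Vh = s² + 0.8/3 + 0.16 × 3²
- Low-risk variance: Vl = s² + 0.8 × 8² + 0.16 × L²
- Model SE / true SE = √{[h·Vh + (1 − h)·Vl] × [1/h + 1/(1 − h)] / [Vh/h + Vl/(1 − h)]}

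With L = 34 weeks (the mean of the 1000-to-300 path) and s = 15, Vh = 226.7 and Vl = 461.2. The ratio is 1.19 at 25% high-risk, 1.00 at 50% and 0.84 at 75%. With s = 26 it is 1.08, 1.00 and 0.93. If the queue stayed long (L = 55, s = 15), it would be 1.32, 1.00 and 0.76.

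The simulations agree. Without drift, coverage of a nominal 95% interval was 97–99.7% at 30% high-risk, 94–96% at 50% and 81–92% at 70%. Robust standard errors gave 94–97%.

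**The case against.** A reader might infer that the estimate corresponds to no real queue, or that the primary result is wrong. Neither follows. When class is unrelated to queue length, the coefficient equals the average difference, which is a fair answer to the stated comparison of patients with and without elevated biomarkers. With no class effect and equal variances neither problem would arise, so the test of no difference is not undermined.

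A reader might also infer that the confidence intervals are wrong. The document does not say that one residual variance will be used. That is only the usual default, and variance structure is commonly left to an analysis plan. Near a 50:50 split the intervals are about right. The only share given is that type 2 inflammation is present in half of asthmatics, and the share among referred patients is not stated. With 1500 patients and L = 34 weeks the true standard error is about 1.0 to 1.7 weeks against a difference of about 25 weeks, so no such miscalibration would reverse the conclusion.

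The size is open to challenge too. The final queue, the throughput and the split by centre are not in the document, and a modest fall gives a modest spread. Some patients go directly to BPT (Figure 2 legend); for them the rule shortens nothing, so an 80% exposure is too high.

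Finally, the plan will describe delays over time by inflammatory status. That shows part of the pattern. But none of the listed subgroup analyses, Kaplan-Meier curves or Cox regression gives the class difference by queue length.

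**Conclusion.** The point stands as a mismatch between the listed model terms and the plan's own scheduling rule. The direction follows from the Intervention section alone: the class difference grows with the queue. The main-effects model reports one average, valid at about the study's mean queue, and forces one queue slope on both classes.

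The size rests on the assumptions above. With p = 0.8 the difference runs from about −39 to −10 weeks if the queue falls to 300 per centre, but only from about −39 to −31 if it falls to 800. It is smaller where non-diagnostic spirometry is less common or patients go directly to BPT. Interval miscalibration is a conditional, secondary matter: too wide when high-risk patients are the minority, too narrow when they are the majority, and negligible near an even split. The change is worth making before analysis, but the primary comparison does not fail without it.

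**What to change.** Add a risk class by number-of-awaiting-tests interaction to the primary mixed model. Report the average class difference together with the adjusted difference at the starting, median and final queue length, each with a 95% confidence interval. Use robust standard errors, or allow a separate residual variance in each risk class, and state which.

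The cost is one extra model term, a variance option and a few lines of analysis text. No new data are needed. The downside is that a short table replaces a single number.

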### Sample size

Approximately 3000 diagnostic tests for suspected asthma are currently pending across the three participating centres (CHUS, CHUSJ and MCH), including around 1500 paediatric tests. Propulsion Santé was funded for 12 months of full-time recruitment (convenience sampling). Based on this pre-existing waitlist and expected referral rates, the Propulsion Santé study aims to recruit 1500 participants aged 6 years and older in the three centres. This sample size will allow us to detect a minimal effect size of 0.07 (Cohen’s f), assuming a significant level of 5%, a power of 80% and a correlation of 0.5 among repeated measures. The calculation was performed using a power analysis for a repeated measures ANOVA with a between-subjects factor in G*Power v 3.1.9.4. Of course, this sample size exceeds our minimum requirement, providing greater assurance in detecting the expected effects, but will also provide a unique opportunity to evaluate diagnostic delays and outcomes in real-world conditions. In addition, the findings will contribute to an ongoing meta-analysis on the diagnostic performance of inflammatory biomarkers.^54^

For the DIVE and DIVE 2 translational substudies (designed prior to PROPULSION SANTÉ), a sample size of 123 participants was originally calculated to provide 90% power to assess the diagnostic performance of three ROC curves. The sample size assumes a 2:1 ratio of asthma-positive to asthma-negative participants, allowing the analysis of three ROC curves, each targeting area under the curve (AUC) values ≥ 0.7, which are significantly different from the null hypothesis (AUC = 0.5), using a two-sided alpha level < 0.016, adjusted for multiple comparisons across three biomarkers.

### Ethics and dissemination

All study protocols have been reviewed and approved by a central Research Ethics Board (#MP-31-2025-5593; MP-31-2024-5346; 2023–4791). The results will be disseminated through presentation at an international conference and publication in a peer-reviewed journal, reported according to the STROBE^55^ and STARD Statements,^56^ and including disaggregation of results according to biological sex and gender.

### Discussion

This study addresses a critical gap in the literature by prospectively evaluating the implementation of inflammatory biomarkers in a real-world primary care referral pathway across both adult and paediatric populations. Beyond its scientific contribution, our protocol will optimise clinical resources by reducing the backlog of approximately 3000 respiratory function tests, currently awaiting completion across the three participating centres, through the engagement of study-dedicated respiratory therapists.

We anticipate that this study will demonstrate the utility of inflammatory biomarkers as effective triage and prioritise instruments for BPT. Given the high rate of false positives in respiratory testing as well as the substantial rate of clinical misclassification in Canada (between 33% and 45% in adults and children),^20 22^ our study will calculate optimal biomarker thresholds to achieve 90% specificity, positive predictive value (PPV) exceeding 80% and LR+ greater than 10—parameters essential for reliable diagnostic confirmation.^57^ In effect, this strategy sacrifices sensitivity in favour of specificity, leading to high PPV and LR+.

Existing literature supports the relevance of our approach. Li *et al* conducted a large retrospective cohort study involving 7463 adult patients with suspected asthma in secondary care. Among the 2349 patients with complete biomarker data, concurrent elevation of FeNO (> 40 ppb) and BEC (>0.3×10ˆ9 cells/L) was associated with a diagnostic specificity greater than 95%.^58^ Similarly, Nekoee *et al* demonstrated that combining biomarkers with spirometry improved diagnostic accuracy (AUC 0.82, 95% CI 0.78 to 0.86),^59^ reinforcing the relevance of inflammometry in routine assessment. Additionally, the predictive value of both BEC and FeNO has been demonstrated in adults,^812 15 16 19 60^,^70^ and to a lesser extent in the paediatric^50^ populations, with significant clinical implications for early intervention and treatment adjustment. Furthermore, these biomarkers are valuable tools for therapeutic decision-making, as elevated values are associated with a better response to anti-inflammatory therapies.^71^,^75^ As modifiable indicators, the inflammatory signals provided by BEC and FeNO highlight the importance of early measurement to better prioritise patients requiring timely inflammation control.^15 61 62 64^

We acknowledge potential methodological limitations. The multicentre design necessitates rigorous harmonisation of practices across sites. The risk of missing data—especially in paediatric patients due to refusal of blood sampling or difficulty in FeNO measurement among children aged 6–8 years—is a concern; this will be minimised by offering a relatively painless capillary blood sampling (which has shown a failure rate below 5%)^76^ or by applying topical analgesia for venipuncture. For FeNO, success rates increase from approximately 40% at age 5 to nearly 100% by age 10.^42 77^ Additionally, the use of 6-s FeNO measurements is expected to further improve feasibility in children aged 6–8 years. Sensitivity analyses using FeNO or blood eosinophils alone will reflect what can be achieved in real-world conditions if one of the biomarkers is not available. Additional limitations include the intrinsic variability of biomarkers related to recent infections or medication use, management of comorbidities that may influence biomarkers and the complexity of economic evaluation across different centres. Nonetheless, this diversity enhances the generalisability of findings across Quebec and potentially other Canadian provinces. Our findings must be contextualised within the evolving landscape of precision medicine in respiratory care. Pavord *et al* have emphasised the clinical and economic benefits of biomarker-guided treatment algorithms in severe asthma, demonstrating reduced exacerbations and improved quality of life through targeted biological therapies.^61^ Similarly, the CAPTAIN study highlighted how biomarker stratification can predict treatment response, potentially transforming clinical decision-making from earlier disease stages.^71^ In this way, our approach brings the principles of precision medicine into the diagnostic process by focusing on identifiable and modifiable traits in an understudied population, that is, individuals with predominantly non-severe asthma issued from the primary/community care. It helps reduce uncertainty in asthma diagnosis by moving from a standard approach to a more personalised assessment using early measurable biological markers.^78^

Our study evaluates the effectiveness of current asthma diagnostic methods in Canada and proposes improvements in Canada. The anticipated outcomes are multifaceted: (1) improved equity in healthcare access through better prioritisation; (2) enhanced patients outcomes by enabling early identification and treatment of individuals with elevated inflammation, thereby reducing exacerbations and lung function decline; (3) organisational and economic efficiency through reduction of costly tests and unnecessary consultations; (4) generation of novel paediatric data; (5) integration of environmental considerations through reduction of inhaler-related emissions.^28 79^

An additional strength of the present project is the integration of two complementary translational substudies—DIVE (in adults) and DIVE 2 (in children)—which provide a unique opportunity to link clinical inflammatory phenotypes with underlying molecular profiles through the collection of NELF and serum samples, and the quantification of key inflammatory proteins (eg, alarmins, interleukins and chemokines). Patients are not pre-selected by T2 phenotype, as these studies are designed as real-world primary care studies. Maintaining the distribution of T2-high and T2-low patients, as observed in the general population, allows assessment of biomarker performance under real-world conditions. These sub-studies will help identify potential biomarkers associated with type 2 inflammation and final asthma diagnosis. By incorporating both paediatric and adult populations, this integrated approach enhances the relevance and applicability of findings and supports the development of precision diagnostic tools that are biologically grounded and clinically actionable.

